**OUTCOMES, INDICATORS AND RESPONSIBLE FOR THE DATA COLLECTION**

| Outcome | Indicator | Responsible for the information collection |
| --- | --- | --- |
| 1. Time in hospital | PCTH Record card | Nurse |
| 2. Number of deaths | Related toTB  Black book, PCTH-Amb Record card, Medical handbook  Related to non-TB  HUCFF’s Medical handbook | Nurse |
| 3. Result of the treatment  (cure, abandonment, treatment failure, change of diagnosis) | Black book , PCTH Record card – Ambulatory | [name] |
| 4. N general adverse effects related to drugs | Medical handbook | Physician |
| 5. N adverse effects related to anti-TB drugs | Medical handbook, PCTH Record card | Physician |
| 6. N adverse effects related to the use of diagnostic methods (i.e.: bronchoscopy, biopsy, induced sputum, etc) | Medical handbook | Physician |
| 7. Time of the diagnosis (in days)  From the randomization to the result release by the Lab | Book of the laboratory - or electronic data in Medtrek | Nurse |
| 8. Time of sensitivity Test | Lab Book / Medtrek | Nurse |
| 9. Time of anti-TB schedule change | PCTH Record card at the end of the 2^nd^ month  PCTH Record card at the end of 6^th^ month | Nurse |
| 10. Proportion of patients with false negative bacteriological result | Medical consultation at the end of the 2^nd^ month | Physician |
| 11. Clinical Worsening | Medical handbook / PCTH Record card 7, 15 30, 60, 180 days | Physician |
| 12. Radiological Worsening | 60 days | Physician |
| 13. Time of symptoms and beginning of the anti-TB treatment | Medical handbook / PCTH  PCTH Record card - Ambulatory and Active Search | Nurse |
| 14. N processed materials until the TB diagnosis | Card registry of the laboratory | Nurse |
| 15. N processed materials after the TB diagnosis | Card registry of the laboratory | Nurse |
| 16. Proportion of patients that develop resistant TB | Laboratory Book - PCTH Record card | Nurse |
| 17. Proportion of bacteriological conversion at the end of the 2^nd^ month | Laboratory Book , Medical Handbook, PCTH Record card | Nurse |

Other information, necessary to analyze the outcomes related to the cost- effectiveness analysis that are not available in the medical handbooks or routine record cards of the Hospital Program will be collected in a standardized way (in annex) by a professional trained at SIA-SUS and in other database of the Ministry of Health and Ministry of Education.

Study forms

- Forms of free and clear consent and of inclusion
- Eligibility forms for selection
- Data collection forms that document the inclusion, the follow-up visits and the specimens collection in the weeks 8 for patients under diagnostic investigation and in the weeks 8, 24 for patients that receive the diagnosis of activeTB.
- Laboratorial form that documents the receiving, processing and results of the clinical specimen.
- Administrative forms that document the participants' deaths, end of the study drugs, direction and adverse events treatment and treatment failures.

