**Excluded patients**

Individuals that do not sign the Term of Free and Clear Consent (or their legal representative) or when there is a refusal of participation. Patients with known active TB

**Study Planning:** Pragmatic, open and randomized clinical trial to be accomplished in two university hospitals in the southeast area of Brazil.

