In patients that receive active TB diagnosis, hepatitis related to drugs monitoring will be accomplished according to the patterns practiced in TB Control Program. Patients that present suggestive symptoms of adverse reactions to drugs will be examined by the doctor and laboratory tests will be carried out, as suitable, including tests of liver function. The physicians of the study will evaluate each case individually to define the relation of the adverse events to the medications of the study. Classification of possible adverse reactions will be made according to NIAID DAIDS *Severity Grading Schema of Adult Adverse Experiences*. The patients diagnosed with possible Grade 3 toxicities related to the drugs, will have the medication that is more likely associated with the adverse event temporarily discontinued. The medication will be resumed when the toxicity is solved. Patients with Grade 4 toxicities will have the medications of the study that are more likely associated with the adverse event permanently discontinued.

Patients considered as in failure of anti-TB treatment shall be treated to the assisting doctor's criterion, according to TB Program routine for these cases. The patients suspicious of treatment failure will be evaluated as for the emergency of TB resistant to drugs and will continue to be followed up clinically and laboratorial according to the protocol agenda until the end of the study.

The participants whose initial culture presented *M*.*tuberculosis* resistant to any of the drugs of the study will be treated with a regimen individually tailored for the susceptibility pattern of the isolated one, as established by the doctors of the study.

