**Secondary outcomes-**

-The secondary outcomes were the mean time to changing the initial clinical prescription,

-The proportion of patients with positive culture and positive smear microscopy for TB,

-The proportion of patients initiating treatment before test results,

-The occurrence of severe adverse events

-Patient satisfaction with the overall treatment- Number of deaths by any cause in the patients included in the study.

- Proportion of patients with TB diagnosis sensitive or resistant to anti-TB medicines (RIF, INH, SM and EMB), with the methods employed in the study.

- Proportion of patients that undergo anti-TB treatment failure during the therapy.

- Proportion of drug resistant TB development in the patients that used the different diagnostic methods and that were classified as treatment failures.

- Proportion of bacteriological conversion (bacilloscopy and culture for mycobacterium) due to the anti-TB treatment at the end of the second and sixth month of anti-TB treatment.

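### The severe adverse event outcome has no limit by cause, but the rows that supply its data count only effects judged related to drugs or diagnostic procedures

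*Protocol*

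**What the plan says.** The list of secondary outcomes that follows section 3.9 includes "The occurrence of severe adverse events". It does not restrict these events by cause and does not say what makes an event severe. The same list has all-cause mortality as a separate item: "Number of deaths by any cause in the patients included in the study".

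Section 3.6, on randomization, says that the information needed to analyse the outcomes will be copied from routine records according to the table that follows it. Three rows of that table concern adverse effects:

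- row 4: "N general adverse effects related to drugs"
- row 5: "N adverse effects related to anti-TB drugs"
- row 6: "N adverse effects related to the use of diagnostic methods"

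A physician collects all three. No row covers adverse events of any cause, and none covers severe events as such.

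Section 3.7 describes attribution: "The physicians of the study will evaluate each case individually to define the relation of the adverse events to the medications of the study". It also describes grading: "Classification of possible adverse reactions will be made according to NIAID DAIDS". Both sentences stand in a paragraph that opens with patients who have received an active TB diagnosis. The synopsis describes the study as a "Pragmatic, open and randomized clinical trial", and under section 3.6 the physician opens the envelope and requests the assigned test.

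**The concern.** The outcome as named and the data planned for it do not match. The name promises all severe adverse events, whereas the table delivers effects that someone has already attributed to a drug or a procedure.

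This matters more in a trial of a diagnostic strategy than in a drug trial. A slower or less sensitive test can harm a patient by leaving disease untreated, and the Rationale and the Hypothesis both name late diagnosis as a problem the new method should reduce. A severe but non-fatal event of that kind is not a drug or procedure effect, so it falls outside this outcome. What remains depends partly on how much drug exposure each arm has, and partly on a judgement of relatedness made with knowledge of the allocation.

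**Working it through.** **1. Trace types of severe event through the planned data.**

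| Severe, non-fatal event | Rows 4–6 | Grading in section 3.7 | Recorded elsewhere |
| --- | --- | --- | --- |
| Reaction to an anti-TB drug | Row 5 | Yes | – |
| Complication of bronchoscopy or biopsy | Row 6 | Not stated | – |
| Deterioration from untreated or late-treated TB | None | No | Row 11 (clinical worsening, days 7 to 180) or row 12 (radiological worsening, day 60); no severity scale stated, and neither is a listed secondary outcome |
| Other illness, not caused by a drug or procedure | None | No | Possibly row 1 (time in hospital) or row 11 |

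If the event is fatal, it enters the mortality outcome. Treatment failure is a listed outcome, but section 3.8 defines it after 5 months of treatment, so it cannot show harm from TB that was missed and left untreated.

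**2. Compare observation times.** Section 3.7 has all patients monitored for 8 weeks, but only those diagnosed with active TB are followed through treatment (24 weeks). The list of study forms agrees: week 8 for patients under investigation, weeks 8 and 24 for those with active TB. Diagnosis comes after randomisation and may differ by arm. Without a fixed window, an arm that diagnoses more patients also has longer observation for drug effects.

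**3. Possible size.** The protocol gives no figure for adverse events, so there is none to reproduce. Its one design figure, 770 participants, is used here only for arm size: 770/2 = 385 per arm if allocation is 1:1 (the ratio is not stated). All other inputs are assumptions:

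- Δt, the difference in proportion treated: 10 points (30% v 40%, or 40% v 50%)
- a, the severe drug-related event rate among treated patients: 3% to 10%
- h, the excess of severe events from late or missed TB in the arm that treats less: 0.5 to 2 points

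Differences are the arm that treats more minus the arm that treats less.

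Related-only difference = Δt × a
- 0.10 × 3% = 0.3 points, or 385 × 0.003 = 1.2 patients
- 0.10 × 10% = 1.0 point, or 385 × 0.010 = 3.9 patients

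All-cause difference = Δt × a − h
- highest: 1.0 − 0.5 = +0.5 points
- lowest: 0.3 − 2.0 = −1.7 points

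The sign changes once h exceeds Δt × a. At a = 5% the break-even is h = 0.10 × 5% = 0.5 points.

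**4. Opposite case.** Suppose the arm that treats more is also the one with more late-TB harm, for example because faster results stop empirical treatment. Then the all-cause difference is Δt × a + h, from 0.3 + 0.5 = 0.8 to 1.0 + 2.0 = 3.0 points. The related-only count then has the right sign but understates the difference. The direction of the error therefore depends on facts the protocol does not give.

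**The case against.** The strongest reply is that the trial keeps disease progression and adverse effects apart by choice, and measures the former well. All-cause death and treatment failure are listed outcomes. The table also collects time in hospital, treatment result, false-negative results, and clinical and radiological worsening. That stands: a reader might infer that the trial cannot see harm from late or missed TB, and the protocol does not support so strong a reading. It does not close the gap, because the worsening rows have no stated severity scale and reach no listed outcome, while the severe adverse event outcome is worded as if it covered every cause.

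A reader might also infer that adverse events are recorded only after attribution. That is too strong. Section 3.7 records symptoms at weeks 2, 4, 8 and 24 and includes scheduled blood tests, the study forms include one that mentions adverse events without a relatedness condition, and grading reaches possible reactions, not only confirmed ones. But the symptom items carry no grade, the adverse-effect checklist is itself framed around drug effects, and the administrative form is not named as a source in the outcome table.

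A third tempting inference is that the outcome penalises MGIT, or can rise only with treatment. The protocol shows neither. Row 6 counts procedure effects, which could be more frequent in the slower arm. The primary outcome counts stopping as well as starting treatment, and the Rationale reports that about 30% to 40% of patients in primary care are treated without bacteriological confirmation, so a faster test could reduce drug exposure. The Hypothesis also names adverse effects among the consequences of late resistance results, so drug toxicity is part of the harm at issue.

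Biased attribution under open allocation is a risk, not something shown. That the rows count events while section 3.11 reports proportions is no contradiction, since summarising counts can be left to the analysis plan. Recording and grading cannot: an analysis plan cannot recover events that were never captured.

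**Conclusion.** The point holds as a mismatch between one secondary outcome and its data source. Followed as written, severe non-fatal events from late or missed TB or other illness would not be counted or graded for this outcome, and the count would depend partly on drug exposure and open-label attribution.

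The direction of any resulting bias is unknown. The illustration, a related-only excess of 0.3 to 1.0 points against an all-cause difference from +0.5 to −1.7 points, rests wholly on assumed rates and on the arm with less treatment having more late-TB harm. It shows that a reversal is possible, not that one will occur. The primary outcome and the sample size are unaffected. The change is worth making because the outcome cannot be repaired at analysis.

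**What to change.** - Define the outcome as the proportion of randomised patients with at least one severe adverse event of any cause, severe meaning DAIDS Grade 3 or higher, over the 8 weeks in which every patient is monitored.
- Reword rows 4–6 so that events are recorded and graded whatever their cause, with relatedness (drug, procedure, TB, other) as a recorded attribute and not a condition for recording. Where possible, judge relatedness without knowledge of the arm.
- Report drug-related events through week 24 separately, for treated patients.

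**Cost.** The outcome table and adverse-event form change, somewhat more has to be extracted from routine records that may not always support grading, and the stated event rates will be higher.

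The 8-week (56-day) window has its own drawback. The Rationale gives 4 to 6 weeks for LJ and 10 to 15 days for MGIT. If treatment starts on the culture result at those times, on-treatment time inside the window is about 8 − 6 = 2 to 8 − 4 = 4 weeks with LJ, against 56 − 15 = 41 to 56 − 10 = 46 days with MGIT. Drug toxicity after a later LJ result is therefore captured less fully, and toxicity after week 8 not at all. The separate report through week 24 recovers those events descriptively, but it compares groups formed after randomisation and should be labelled so.

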**3.6. Data obtainment**

All of the forms will be created in Word, and the data will be included in the ACCESS database. All the data will be filled out according to the instructions that will be defined and detailed in a specific manual. The patients' names shall be collected only once and this information will be kept separately in a form that does not contain clinical or laboratorial data. The number of the patient's identification will be used in all of the forms that contain results. The evaluation of the clinical data quality will be accomplished twice a year, and 10% of the patients included in the 6 previous months will have all the primary and computerized results revised.

**3.6.1.-Storage and filing of the registrations**

The director of the study, [name], and the data manager will be responsible for keeping the storage of all of the used source registries and to fill out the forms of the study data survey. The source registries may include requests and laboratorial reports, clinical notes and documentation of the references. All the forms of the study data survey and source registries will be stored in files locked in a safe area. All the information of the locater will be maintained in locked rooms in a safe area and separate from all the other documents of the study. The access to the data files and the study registries will be limited to the study personnel.

**3.6.2 - Data handling**

An original ID number of the study will be attributed to each participant. This number will be registered in each data form and clinical specimen to facilitate the data network. Names and other obvious identifiers shall not be used in forms, and will only be used in the clinical specimens that are collected during non-programmed visits of the clinic for immediate care. If necessary, the questionnaires and the specimens will be identified by a two digit number of visit, by a one digit code for type specimen, and by a one digit code that identifies the aliquot of the specimen for deposited specimens of the sputum. To minimize transcription mistakes and to assure that each instrument of the data survey and each specimen will be correctly labeled, the pre-printed labels with the ID number and the participant's name will be generated to label each form and specimen.

The manager of the place will keep follow-up books to register the dates of the clinic visits made, the ones to come, as well as the dates of specimens collection. In addition, for each patient a study file will be kept, containing all the forms, laboratory results and other information pertinent to the study. All of the follow-up books and registrations will be kept in filing closets, locked when not in use and accessible only for the clinical personnel.

The laboratory tests will be requested in the requisition forms of the study’s test laboratory that are printed on a pressure sensitive paper, of multiple sheets. In the laboratory, the test results will be registered on the requisition form and the sheets will be separated and distributed as follows: the bottom sheet stays at the laboratory, the middle sheet is returned to the clinic and the top sheet goes to the computer room for data insertion.

**All the finished questionnaires will be collected daily from the clinic and introduced into the computer within 72 hours.** An adapted system of double entry will be used to computerize all of the study instruments. The forms received at the computer room will be received under receipt. The forms will be incorporated and verified, and the date of these procedures will be registered on the reception sheet. The data files will be verified so as to see if there are logical and scale mistakes using adapted SPSS programs.

The identification number (ID), the collection date, the specimen volume and the position in the freezer will be registered on the requisition forms of the laboratory and introduced into the computer for all the deposited specimens. The computer files of these forms will be used to create specimen lists for each box of specimens. Two years after the conclusion of the study, the identifiers, excluding the ID number of the study, will be suppressed from the computerized data files and from the paper files.

**3.7. The patient's evaluation during the diagnostic investigation phase (total of 8 weeks) and anti-TB treatment (total of 24 weeks)**

All the patients will be clinically evaluated and continually monitored during the first 8 weeks of the diagnostic investigation phase. Those who receive an active TB diagnosis will be monthly monitored until the end of the drug treatment. The information below, collected in the routine follow-up of the Hospital Tuberculosis Program, will be obtained in the weeks 2, 4, 8, and 24 will be registered in the forms of the study:

▪ Weight

▪ Signs and symptoms associated with TB (e.g. cough, fever, sweating, weight loss, haemoptysis)

▪ Signs and symptoms associated with adverse effects of the drugs of the study (e.g. cutaneous rash, dizziness, fatigue, weakness, anorexia, nauseas, vomiting, diarrhea, abdominal flabbiness, jaundice, neuropathy, palpitations)

▪ If a patient develops new signs or of worsening and symptoms of pulmonary TB, a new chest teleradiography will be performed and three sputum specimens shall be obtained for TB culture and sensitivity tests. If a patient develops signs and symptoms of extra-pulmonary TB, cultures from the appropriate places of the body will be obtained.

Monthly evaluations in the weeks 4 and 24 will include the above indicated procedures and:

▪ A complete hemogram (blood count) with platelet count, creatinine, ALT, AST, Gamma GT, total bilirubin and fractions and alkaline phosphatase

▪ Sputum specimens (2) for direct bacilloscopy (Baar research) and culture for mycobacterium

▪ If a patient is unable of producing sputum naturally, the sputum shall be induced by hypertonic saline solution inhalation

▪ A chest radiography performed in week 8

▪ Drugs sensitivity test accomplished in weeks 8 and 24

In patients that receive active TB diagnosis, hepatitis related to drugs monitoring will be accomplished according to the patterns practiced in TB Control Program. Patients that present suggestive symptoms of adverse reactions to drugs will be examined by the doctor and laboratory tests will be carried out, as suitable, including tests of liver function. The physicians of the study will evaluate each case individually to define the relation of the adverse events to the medications of the study. Classification of possible adverse reactions will be made according to NIAID DAIDS *Severity Grading Schema of Adult Adverse Experiences*. The patients diagnosed with possible Grade 3 toxicities related to the drugs, will have the medication that is more likely associated with the adverse event temporarily discontinued. The medication will be resumed when the toxicity is solved. Patients with Grade 4 toxicities will have the medications of the study that are more likely associated with the adverse event permanently discontinued.

Patients considered as in failure of anti-TB treatment shall be treated to the assisting doctor's criterion, according to TB Program routine for these cases. The patients suspicious of treatment failure will be evaluated as for the emergency of TB resistant to drugs and will continue to be followed up clinically and laboratorial according to the protocol agenda until the end of the study.

The participants whose initial culture presented *M*.*tuberculosis* resistant to any of the drugs of the study will be treated with a regimen individually tailored for the susceptibility pattern of the isolated one, as established by the doctors of the study.

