**3.8. Definition of a TB Suspect Case, Active TB Case and Discordance Analysis**

**Pulmonary and /or pleural pulmonary form**

Every patient under pulmonary TB suspicion that presents respiratory signs/symptoms and with alterations in the chest X-ray will be classified in three groups;

a) Typical pattern of TB: infiltrated in upper third (LS or apical seg of LI), with or without cavity; bilateral miliar infiltration; unilateral pleural hemorrhage with upper lobe infiltration .

b) Intermediate pattern of TB: infiltrated in middle or lower third, with or without cavity in these areas; isolated pleural hemorrhage, infiltrated in upper thirds of undetermined activity; diffuse abnormalities (not miliar); mediastinal or hilar enlargement .

c) Atypical Pattern of active TB: multifocal hypotransparency images; alveolar hypotransparency images; calcified nodules.

“**Confirmed TB case"** will be defined as the patient with at least one positive culture for *M. tuberculosis* in L-J or MGIT960*.*

**“Probable TB case"** will be defined as the patient that presents negative results to culture with one or more of the following characteristics:

a) clinical answer to the treatment (defined as improvement to X-ray, b) decrease of the cough and 3% weight gain in relation to the beginning of the treatment) and absence of alternative diagnosis;

Patient not classified as confirmed case or probable TB will be considered "non- TB."

**Treatment failure:** patient that remains with positive bacteriological test (two samples in a 30 day interval) after 5 months of treatment, standardized by MH

High risk factors for resistant TB:

a) Relapsing TB (previous complete treatment for TB with apparent cure), b) Treatment failure (patient under treatment ≥ 4 months with positive bacilloscopy), c) Patient’s contact with multidrug resistant-TB.

3.9 **Main outcome**  The primary outcome was defined as the proportion of patients in each group whose initial prescription changed by the second month after randomization. The ‘change’ could be initiating or stopping TB treatment.

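### Scheduled follow-up after week 8 depends on a TB diagnosis that the allocated culture can influence, yet deaths and severe adverse events are compared between arms with no common time window.

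*Protocol*

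**What the plan says.** - **Follow-up (section 3.7).** "All the patients will be clinically evaluated and continually monitored during the first 8 weeks of the diagnostic investigation phase". After that, "Those who receive an active TB diagnosis will be monthly monitored until the end of the drug treatment". The section heading gives the treatment phase as "anti-TB treatment (total of 24 weeks").
- **Forms (Study forms list, after the outcomes table).** Data collection is planned "in the weeks 8 for patients under diagnostic investigation and in the weeks 8, 24 for patients that receive the diagnosis of activeTB".
- **Case definition (section 3.8).** A confirmed case "will be defined as the patient with at least one positive culture for" *M. tuberculosis*, by either method. A culture-negative patient can be a probable case through response to treatment with no alternative diagnosis. Section 3.5 randomises the culture method.
- **Outcomes (Secondary outcomes list).** "Number of deaths by any cause in the patients included in the study" and "The occurrence of severe adverse events", neither with a time window. The primary outcome (section 3.9) does have one, the second month after randomisation, for all patients.
- **Sources (outcomes table, row 2).** TB-related deaths come from three record sources. Non-TB deaths come from the university hospital's medical handbook only. No date limit is given. Section 3.1 lists two sites.
- **Analysis (section 3.11).** Relative risk, risk difference and number needed to treat, by intention to treat.

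**The concern.** A comparison of event counts between randomised arms is fair only if the arms are observed for the same time and in the same way. Here, active observation from week 8 to week 24 depends on being diagnosed with TB. That status arises after randomisation and is one that the culture method may change. The effect measures named in section 3.11 make no allowance for unequal observation.

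Death capture from records does not clearly repair this. More sources are listed for TB-related deaths than for other deaths, and the only source for the latter belongs to one of the two sites. Capture after week 8 may therefore also depend on TB status.

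At stake is the reading of the safety and mortality results. Section 2 hypothesises a large reduction in morbidity and lethality. A difference in observation time could hide part of such a benefit, or imitate benefit or harm, depending on which arm diagnoses more patients.

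**Working it through.** The protocol gives no figure for this comparison. Its sample size of 770 concerns the primary outcome and is used here only for the arm size. With 50% v 40% assumed, two-sided 5% and 80% power, n per arm = (1.960 + 0.842)² × (0.25 + 0.24) / 0.10² ≈ 385, so 770 in total (1:1 assumed).

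**Inputs from the protocol:** 8 weeks of monitoring for all; 24 weeks if TB is diagnosed, counted here from randomisation. If treatment starts later, the gap is wider.

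**Assumed inputs:** share diagnosed p in each arm; one constant weekly death hazard h, identical in all patients and both arms; no deaths counted after week 8 in undiagnosed patients (relaxed below).

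**Observed time.** Mean weeks = 8(1 − p) + 24p = 8 + 16p. Each 10-point difference in p adds 1.6 weeks per patient.

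**Counted risk.** R(p) = (1 − p)(1 − e^(−8h)) + p(1 − e^(−24h)). At h = 0.5% per week the two terms are 1 − e^(−0.04) = 0.0392 and 1 − e^(−0.12) = 0.1131. For p = 0.30, R = 0.70 × 0.0392 + 0.30 × 0.1131 = 0.0614. For p = 0.40, R = 0.60 × 0.0392 + 0.40 × 0.1131 = 0.0688.

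| Share diagnosed | Mean weeks | Counted risk (h = 0.5%) | Deaths per 385 | Spurious RR |
|---|---|---|---|---|
| 30% v 30% | 12.8 v 12.8 | 6.14% v 6.14% | 23.6 v 23.6 | 1.00 |
| 20% v 25% | 11.2 v 12.0 | 5.40% v 5.77% | 20.8 v 22.2 | 1.07 |
| 20% v 30% | 11.2 v 12.8 | 5.40% v 6.14% | 20.8 v 23.6 | 1.14 |
| 30% v 40% | 12.8 v 14.4 | 6.14% v 6.88% | 23.6 v 26.5 | 1.12 |

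Across h = 0.25% to 1% per week and the three unequal pairs, the spurious RR runs from 1.07 to 1.14.

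**Partial capture.** Suppose records pick up half of the later deaths in undiagnosed patients. Their counted risk becomes 0.0392 + 0.5 × (0.1131 − 0.0392) = 0.0762. Then 30% v 40% diagnosed gives 0.70 × 0.0762 + 0.30 × 0.1131 = 0.0873 against 0.60 × 0.0762 + 0.40 × 0.1131 = 0.0910, RR about 1.04.

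**Against sampling error.** For 6.14% v 6.88% at 385 per arm, the standard error of the difference is √[(0.0614 × 0.9386 + 0.0688 × 0.9312) / 385] = 0.0178. The artefact of 0.0074 is about 0.4 standard errors.

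**With a common window.** At 8 weeks for everyone, the risk at h = 0.5% is 3.9% in both arms, RR 1.00, whatever the shares diagnosed.

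**The case against.** A reader might infer that the randomised test decides who is followed, that the MGIT arm must therefore show more deaths, and that the bias runs against the trial's hypothesis. The protocol does not support this:

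- Probable TB is set by clinical response, and treatment before test results is expected, since it is itself a secondary outcome. The test influences diagnosis; it does not decide it.
- The synopsis describes MGIT accuracy as similar to solid culture, and the Rationale puts solid-culture incubation at 4 to 6 weeks, normally inside the 8 weeks of common follow-up. The shares diagnosed could be close, and the primary outcome counts stopping as well as starting treatment.
- Deaths are taken from records with no date limit, so later deaths in undiagnosed patients are not plainly lost.
- An arm that treats more patients will have more drug reactions. In a comparison of strategies, that part of any excess is a real effect.
- The artefact is small beside sampling error in every case computed above.

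These points limit direction, size and wording, and all of them stand. They do not make observation equal. Nothing in the protocol ensures that undiagnosed patients' later events are captured as diagnosed patients' are, and the record sources differ by TB status. It could also be said that an analysis plan may set the window. It could restrict the comparison to week 8, but it cannot supply week-24 forms that the protocol's schedule does not collect from undiagnosed patients.

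**Conclusion.** The concern holds as a conditional bias in two secondary outcomes. Followed as written, the plan can compare deaths and severe adverse events over unequal observation time, driven by a post-randomisation status that the allocated culture can influence.

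For deaths, the spurious RR is about 1.07 to 1.14 under the assumed shares and equal hazards. It is lower with partial capture of later deaths and 1.00 with equal shares. The shares and hazards are assumptions, because the protocol gives neither. No figure is offered for adverse events, where artefact and real drug toxicity would be mixed. Which arm would be disadvantaged is not established. The primary outcome and the sample size are not affected.

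**What to change.** In the Secondary outcomes list, define the between-arm comparison of all-cause deaths and of severe adverse events as events within 8 weeks of randomisation in all randomised patients. State that later events in TB patients are reported descriptively.

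For the lethality hypothesis in section 2, add a comparison of deaths to week 24 only if vital status is taken from existing records at both sites, in the same way for every randomised patient. Row 2 of the outcomes table should then name the same sources and the same date limit for TB and non-TB deaths.

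The 8-week definition costs a sentence or two and needs no extra visits or patients. The week-24 option adds a record check at both sites. The downside of the 8-week window is that later events in TB patients leave that randomised comparison. This includes events after late resistance results: solid culture takes 4 to 6 weeks and the proportions test incubates for a further 28 days, so those results fall at about weeks 8 to 10. The uniform week-24 death comparison is the way to recover that period for mortality.
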